### Self-management exercise program

The main objective of the self-management exercise program will be to allow people to understand the importance of physical exercise practice and learn when, where and how to practice exercise, in order to adapt their PA practice according to their phenotype and integrate it long term in their daily life.

Each session will consist of 45 min of self-management education and 45 min of PA practice, with aerobic training program, strength training, range of motion and personal feedback. The exercise program will be tailored to each participant. The physiotherapist or adapted PA instructor will drive an experimental arm of 5 to 7 participants. The 5 sessions will take place on days (D) D4, D7, D10, D13 and D16.

For each workshop, a specific objective and operational objectives are defined, linked to criteria and indicators (Table 1).

**Table 1 Tab1:** Self-management education program

Session	Objectives
Session 1: ᅟEvaluate the representation of the patient’s PA	- Identify the representation of PA
	- Identify the barriers to and facilitators of regular PA practice
	-Acquisition of knowledge about OA
	-Know the methods of the exercise practice
Session 2: ᅟDefining the importance of exercise in knee OA	-Name the benefits of PA in the management of knee OA
	-Identify the normal and abnormal physiological signs during the PA practice
	- Learn to adapt the exercise according to its knee OA (intensity, duration)
Session 3: ᅟPatient engagement in regular PA practice	- Determine where, when and how to exercise throughout the year
	- Include an exercise program in everyday life
	- Know the anatomical bases necessary for performing the adapted exercises
Session 4: ᅟThe consequences of stopping the exercise program	-Know the importance of maintaining exercise program on a regular and long-term basis
	-Identify factors that could facilitate or limit the continuation of the exercise program
	-Learn how to build a PA session
Session 5: ᅟKnowledge restitution	- Know the means of managing knee OA
	- Know how to live healthy with knee OA
	-Set an achievable goal

*PA* physical activity, *OA* osteoarthritis

To facilitate the workshops, different teaching tools and techniques will be used: paper board, thematic discussion, participative discussion, practical leaflets (Borg scale, deconditioning circle), information booklet, exercise demonstration, feedback, and pain coping skills.

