### Interventions

Both groups will receive 18 sessions of STT over 3 weeks and an education booklet on the benefits of PA practice illustrated with pictures and a detailed description of the exercises to perform (Additional file 1). Only the experimental group will receive the self-management exercise program. The aim is to propose a reinforcement of the STT effect through a self-management exercise program.

The STT and the self-management exercise program will be standardised and designed by expert spa therapy physicians.

Interventions have been designed by a specialist steering committee, standardized and reproducible for the 3 centers. The steering committee consists of investigators, a spa therapist, physician and physiotherapist and the university hospital’s medical team (physician, physiotherapist, adapted PA instructor).

Meetings with all members of the steering committee are organized to obtain consensus on the therapeutic protocol describing precisely the content and the organization of the intervention taking into account the context and the expertise of the different centers involved in the study.

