### SPA therapy treatment

Each spa therapy session will comprise a mineral hydrojet session at 37 °C for 15 min, the thigh manipulated under mineral water at 38 °C by a physiotherapist for 10 min, manual massages, the application of mineral-matured mud at 45 °C to the knees for 15 min and supervised general mobilisation in a collective mineral water pool at 32 °C in groups of 8 patients for 15 min of 18 sessions, for 1 h each.

The main component of mineral waters are chlorobarbonated sodium in Royat (63) and Le Mont-Dore (63) spas centers and sodium chlorides in Bourbon Lancy (71).

Both groups will be mixed with the general public in the spa center. The spa therapist will not be aware of which patients will be taking part in the clinical trial.

The experimental and active comparator arms will receive unrestricted non-pharmacological, pharmacological and usual care during the study. Medication taken during or after the intervention will be reported in the follow-up questionnaires.

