### Statistical considerations

#### Sample size estimation

According to previous works presented in literature [11], we have estimated that a sample size of *n* = 65 patients per randomized group, for a two-sided type I error at 5%, would provide 80% statistical power of detecting an absolute difference of 20% (25% vs 5.) in the primary outcome: proportion of participants varying to one IPAQ class at least (low-moderate or high or moderate-high). Finally, a total of *n* = 142 patients (71 by group) will be considered to take into account lost to follow-up (10%).

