#### Statistical analysis

Statistical analyses will be conducted using SAS software (version 9.3.). A two-sided *p*-value of less than 0.05 will be considered to indicate statistical significance (except interim analysis).

Concerning the primary outcome, the comparison between groups will be analysed using Chi-squared or Fisher’s exact tests. Intention to treat (ITT) analysis will be considered for the primary outcome. Then, the analysis of the primary outcome will be completed by multivariate analysis using a generalized linear mixed model (logistic for dichotomous dependent endpoint) to take into account: (1) fixed effects covariates determined according to univariate results and to clinical relevance (for example gender, age and analgesic treatments), and (2) centre as random-effects (to measure between and within centre variability). Continuous endpoints will be compared between groups using Student’s t-test or Mann-Whitney’s test. Normality will be studied by the Shapiro-Wilk test and homoscedasticity using the Fisher-Snedecor test. As suggested by Vickers and Altman [40], the comparison between groups will be completed by linear mixed model considering randomization group and baseline values as independent parameters (fixed effects). Other categorical parameters will be analysed as described previously. Longitudinal analyses concerning repeated measures (for example ASES, KOFBeQ, WOMAC, EVA pain, fears and beliefs, assessed at baseline, after intervention and 3 months after intervention) will be studied using random-effect models (linear or generalized linear), to take into account patient as random-effect (slope and intercept), nestled in centre random-effect, while studying the fixed effects group, time and group *interaction x time*.

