## Discussion

In the context of an aging population, OA is a high-prevalence disease, whose prevalence will increase in the future [41]. In addition, OA is not limited to joint pain and stiffness, and the health care strategy needs to be standardized and personalized with optimized adherence to treatment [42]. This research question is important because OA lacks a cure, and few solutions to the management of knee OA are offered to patients. Treatments will be based on modifiable risk factors, such as pain, function, obesity, comorbidities, intrinsic barriers to PA practice, and sedentary time [43, 44]. The knee OA population appears to be more affected by these risk factors [45, 46], and the most severely affected patients are the less active ones [12]. The key challenge for OA treatment consists in increasing PA level to decrease the risk factors [47].

This quasi-randomized trial will be the first study to compare the effect of a self-management exercise program associated with spa therapy versus spa therapy alone. The non-invasive, adapted, tailored and original character of the intervention is a novel approach for knee OA management.

STT can improve pain and functional capacity of people with knee OA [14]. PA practice must be the key element in managing knee OA symptoms, according to recommendations [8]. However, many obstacles to exercise have been described [48], such as fears and beliefs about pain, treatment and PA [49]. Hence, changing the PA behaviour of people with knee OA is difficult [50]. Education and self-management are based on the bio-psycho-social model, effective strategies for modifying fears and beliefs and increasing adherence to treatment [51].

This protocol has some limitations. The quasi-randomized method could be a limitation, but this method is the most appropriate to avoid contamination biases between groups [29]. When assessing the effectiveness of non-pharmacological treatments such as behavioral therapy the blinding of participants and care providers is frequently impossible [52–54]. Moreover, the success of the treatment often depends on the skill and experience of care providers [26, 55, 56].

The study could demonstrate that self-management exercise programs offer a complementary therapy to the spa therapy effect could reinforce in the medium term increasing PA level and could ameliorate fears and beliefs, self-efficacy and anxiety/depression.

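### The programme is delivered in groups of 5 to 7 in the experimental arm only, but no specified test or model has a session-group level; if outcomes correlate within groups, standard errors are understated

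*Protocol article*

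**What the plan says.** The Interventions section limits the programme to one arm: "Only the experimental group will receive the self-management exercise program". Under Self-management exercise program, each group has a leader and a size: "The physiotherapist or adapted PA instructor will drive an experimental arm of 5 to 7 participants". There are five sessions of education and exercise between day 4 and day 16, and the teaching methods include participative discussion. Both arms also use the spa pool, described as "supervised general mobilisation in a collective mineral water pool at 32 °C in groups of 8 patients", but there they are mixed with the general public.

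The Statistical analysis section names the methods. The primary comparison is a chi-squared or Fisher's exact test, followed by a logistic mixed model with centre as the random effect. Continuous outcomes are compared by t-test or Mann-Whitney test, then by a linear mixed model with arm and baseline value as fixed effects. Repeated measures use models intended "to take into account patient as random-effect (slope and intercept), nestled in centre random-effect". The word group in these models means the randomised arm. No session-group term appears.

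The Sample size estimation section states that "65 patients per randomized group, for a two-sided type I error at 5%, would provide 80% statistical power" for an "absolute difference of 20% (25% vs 5"%, with 71 recruited per arm. It includes no design effect.

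**The concern.** Patients who share sessions, discussion and a leader may end up more alike than patients who do not. The primary outcome, a change of physical activity class, is a behaviour that such sessions aim to shift. The Discussion also remarks that "the success of the treatment often depends on the skill and experience of care providers". Control patients have no session group, so this clustering exists in one arm only. It comes from how the treatment is delivered and would remain under individual randomisation.

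Three centres shared by both arms cannot represent correlation within 10 to 15 small groups in one arm. If that correlation is positive, the unclustered analyses give too small a standard error for the primary outcome and for self-efficacy, fears and beliefs, and anxiety and depression. A few well-run groups could then be read as an effect of the programme. Because the section names its random effects, this is a stated specification rather than a detail left open.

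**Working it through.** **Inputs from the protocol article.** Session groups of 5 to 7 (Self-management exercise program); 25% versus 5%, two-sided 5%, 65 evaluable and 71 recruited per arm (Sample size estimation). Number of session groups: 71/7 = 10.1 to 71/5 = 14.2, so about 10 to 15.

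**Assumed, because the documents give no figure.** Session-group ICC of 0.02, 0.05 and 0.10 (0.20 as an extreme); stable group membership; groups of 6 as the central case.

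**The plan's own figure.** With the pooled-variance formula, n = [1.96·√(2·0.15·0.85) + 0.842·√(0.1875 + 0.0475)]² / 0.20² = 48.8, so 49 per arm for 80% power (59 with continuity correction). The stated 65 is the result for 90% power (64.9). That mismatch is a separate matter. Here it means only that there is some slack.

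**Design effect, experimental arm only.** DE = 1 + (m − 1)·ICC. With m = 6 it is 1.25 at ICC 0.05 and 1.50 at ICC 0.10.

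**Interval at 25% versus 5%, 65 per arm.** Half-width = 1.96·√[(0.1875·DE + 0.0475)/65].

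| ICC | DE | Half-width (points) | Ratio to unclustered | Actual coverage of a nominal 95% interval |
|---|---|---|---|---|
| 0 | 1.00 | 11.8 | 1.00 | 95% |
| 0.05 | 1.25 | 12.9 | 1.095 | about 93% |
| 0.10 | 1.50 | 13.9 | 1.183 | about 90% |

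Coverage is the normal probability within ±1.96/ratio: ±1.79 and ±1.66.

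**Type I error, chi-squared.** Beta-binomial simulation, 11 groups of 6 against 66 independent controls, no month effect:

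| Common rate | ICC 0 | 0.02 | 0.05 | 0.10 |
|---|---|---|---|---|
| 5% | 4.7% | 5.2% | 6.0% | 7.4% |
| 15% | 4.8% | 5.3% | 6.2% | 7.7% |
| 25% | 4.9% | 5.5% | 6.4% | 7.9% |

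A second simulation with 65 per arm and nominal group sizes of 5 to 7 gives 5.8 to 7.1% at ICC 0.05 and 6.8 to 9.0% at ICC 0.10.

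**Type I error, Fisher.** In that second simulation:

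| Common rate | ICC 0.05 | 0.10 | 0.20 |
|---|---|---|---|
| 5% | 1.5 to 1.8% | 2.1 to 2.6% | 3.0 to 4.2% |
| 15% | 3.7 to 4.3% | 4.5 to 5.5% | 6.1 to 8.8% |
| 25% | 4.1 to 4.4% | 4.9 to 6.0% | 6.9 to 9.3% |

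With a common 5% rate the expected number of responders is 65 × 0.05 = 3.25 per arm, where Fisher's test is the usual choice.

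**Power.** With 65 per arm and a test that allows for the session groups, power for 25% versus 5% is 85 to 86% at ICC 0.05 and 79 to 83% at ICC 0.10 (m = 5 to 7, normal approximation). This leaves out any centre-month effect and the loss of degrees of freedom.

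**Cluster-level check.** If each session group is one cluster and cluster means are compared, pooled-variance type I error is 4.9 to 5.3% with equal numbers of clusters per arm and 3.7 to 4.1% with unequal numbers. Welch's version gives 4.6 to 4.8% with unequal numbers.

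**The case against.** A reader might infer that type I error does exceed 5% and that the planned intervals are too narrow. The documents do not support either as a fact. Both need a session-group ICC above zero, and none is given. At 0.02 the chi-squared error is only 5.2 to 5.5%. Fisher's test, which the plan allows, stays below 5% at the planned control rate. The section also specifies no interval for the primary difference, so the one computed above is simply the interval that goes with an unclustered comparison. These limits stand. Fisher's conservatism, however, is no protection for the chi-squared test, the t-tests, the mixed models or an interval.

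Nor do the documents say that one instructor leads every group, or that membership is fixed. The programme is standardised and tailored to each participant, which argues for a low ICC, and the remark on provider skill is a general one. Standardised content still does not remove the influence of peers.

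The strongest objection concerns overlap. Arms alternate by month within centre, so the centre-month is a cluster in both arms and is also missing from the models. Session groups probably lie within experimental centre-months, or coincide with them; that is an inference. A cluster-level centre-month analysis would then absorb most of this problem. That is right and shapes the fix, but no such term is planned. It also means that a model treating each control patient as independent would be inadequate here.

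**Conclusion.** The point holds in conditional form. Group delivery in one arm is stated, and every named test and model omits that level. With groups of 6 and an assumed ICC of 0.05 to 0.10, the interval should be about 10 to 18% wider, coverage of a nominal 95% interval is about 93 to 90%, and chi-squared type I error is about 6 to 8%. At an ICC of 0.02 or below the effect is slight. Fisher's test passes 5% only marginally at ICC 0.10 with rates of 15 to 25%, and clearly only at 0.20. The figures rest on the assumed ICC, stable groups and no additional month effect. The change is worth making because it is cheap and because the correction may be impossible later if group membership is not recorded.

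**What to change.** Record the session-group identifier and the group leader for every experimental patient. Base the test and interval for the primary difference, and for the continuous secondary outcomes, on an analysis with the centre-month allocation block in both arms plus a session-group effect in the experimental arm, with arm-specific variance and small-sample degrees of freedom.

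If session groups coincide with experimental centre-months, a simpler analysis is enough: a centre-month cluster-level comparison with unequal variances (Welch), or cluster-robust standard errors with a small-sample correction. It also avoids relying on a session-group variance component that will often be estimated as zero. With 11 groups of 6 and a binary outcome, the analysis-of-variance estimate was zero or negative in 38 to 47% of simulated trials at ICC 0.05 and in 23 to 37% at ICC 0.10.

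The cost is one or two recorded identifiers and revised analysis wording. The downside is a wider interval and a less favourable p-value if the ICC is positive.

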### Education booklet

Patients will receive an information booklet containing cards with physical exercises adapted to their pathology to integrate the exercise program into their daily routine. This booklet will contain information about the pathology and PA practice with knee OA and illustrated cards with detailed descriptions of the exercises to be practiced (Additional files 1 and 2).

### SPA therapy treatment

Each spa therapy session will comprise a mineral hydrojet session at 37 °C for 15 min, the thigh manipulated under mineral water at 38 °C by a physiotherapist for 10 min, manual massages, the application of mineral-matured mud at 45 °C to the knees for 15 min and supervised general mobilisation in a collective mineral water pool at 32 °C in groups of 8 patients for 15 min of 18 sessions, for 1 h each.

The main component of mineral waters are chlorobarbonated sodium in Royat (63) and Le Mont-Dore (63) spas centers and sodium chlorides in Bourbon Lancy (71).

Both groups will be mixed with the general public in the spa center. The spa therapist will not be aware of which patients will be taking part in the clinical trial.

The experimental and active comparator arms will receive unrestricted non-pharmacological, pharmacological and usual care during the study. Medication taken during or after the intervention will be reported in the follow-up questionnaires.

### Measures

At baseline, we will collect data on sociodemographic items (age, Body Mass Index (BMI), marital status, area living, education status), anthropometric measures (Bioimpedance, Short Physical Performance Battery, Handgrip) and co-morbidities association, according to OARSI guidelines [7] (diabetes, hypertension, cardio vascular disease, renal failure; gastrointestinal (GI) bleeding, depression, or physical impairment limiting activity, including obesity).

#### Primary outcomes

The primary outcome is the proportion of participants varying to one IPAQ class at least (low-moderate or high or moderate-high) at 3 months [28]. The IPAQ short form (International Physical Activity Questionnaire) is a self-administered questionnaire which measures the physical activity level of people in a heterogeneous population as well as knee osteoarthritis people [31].

#### Secondary outcomes

● The arthritis self-efficacy influence on pain, function and other symptoms is assessed with the Arthritis Self-Efficacy Scale (ASES) [32] validation in French language is in progress NCT: 02977325 [33].

● Fears and beliefs changes are measured by the Knee OA Fears and Beliefs Questionnaire (KOFBeQ) [34].

● Physical function is assessed by the Western and McMaster Universities Osteoarthritis Index (WOMAC subscale for physical function (W-TPFS)) [35, 36].

● Pain intensity during the last 24 h and the worst pain intensity during the last month are measured by a numerical pain scale.

● Overall psychological status is assessed by the Hospital Anxiety and Depression Scale (HAD) [37, 38].

● The barriers to and facilitators of regular PA practice are assessed by 24 independent and specific items designed by a qualitative study [39], specifically for this study because of no reference scale. Each item will be coded from 0 (strongly disagree) to 4 (strongly agree). The prospective validation of this new scale is in progress.

● Use of pharmacological treatment is recorded (paracetamol, opioids, NSAIDs, intra-articular corticoid/hyaluronic acid).

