### Time-point outcomes

Study outcomes will be collected at baseline and after treatment (18 days) in spa resorts and at 3 months post-randomisation, by mailed self-reporting questionnaires. If needed, the research officer will use a telephone follow-up.

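### Asked at the 18-day visit, worst pain in the last month includes about 12 pre-treatment days, so it understates any between-arm difference at the end of treatment (minor)

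*Protocol article*

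**What the plan says.** The Secondary outcomes section of the protocol article defines two pain items on a numerical scale. The first is "Pain intensity during the last 24 h". For the second, "the worst pain intensity during the last month are measured by a numerical pain scale".

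The visit schedule is under Time-point outcomes: "Study outcomes will be collected at baseline and after treatment (18 days) in spa resorts and at 3 months post-randomisation". It names no outcome as left out of a visit and gives no shorter recall period for 18 days.

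The Statistical analysis section lists examples of repeated measures, including "EVA pain, fears and beliefs, assessed at baseline, after intervention and 3 months after intervention". These go into random-effect models with group, time and their interaction. The list does not say which of the two pain items is meant by EVA pain.

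Two statements fix the timing of treatment. Under Interventions: "Both groups will receive 18 sessions of STT over 3 weeks". Under Self-management exercise program: "The 5 sessions will take place on days (D) D4, D7, D10, D13 and D16".

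The Aim section places the pain objective at 3 months. Only sarcopenia is tied there to the end of treatment at 18 days.

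**The concern.** The recall window of the worst-pain item is longer than the time between the baseline and end-of-treatment visits. A patient who answers at 18 days reports on the treatment period and also on days before treatment began. The baseline answer has already scored those days.

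For an average, such an overlap would dilute the change roughly in proportion to the overlapping days. For a maximum it does more. One bad day before treatment sets the score, however much pain fell afterwards, and the more pain falls during treatment, the more often the reported worst day lies before it.

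Two readings of the results could then mislead. The group-by-time contrast at 18 days would be pulled towards no difference, suggesting that worst pain did not respond during the stay. The change from 18 days to 3 months would include an apparent late gain that arises only because the pre-treatment days have dropped out of the window.

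**Working it through.** The article states no figure for this point, so there is none to reproduce. The check is date arithmetic followed by an illustration.

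**Inputs from the article.** Recall of one month (taken as 30 days, varied from 28 to 31). Visit at 18 days, or at 21 days if it falls at the end of the 3 weeks. First experimental session on D4. The baseline answer is assumed to be given at the start of treatment.

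**Pre-treatment days in the window** = recall length − days from start of treatment to the visit.

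- Visit at 18 days: 30 − 18 = 12 days; 12/30 = 40% of the window.
- Visit at 21 days: 30 − 21 = 9 days; 9/30 = 30%.
- Extremes: 28 − 21 = 7 days and 31 − 18 = 13 days.

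The window starts before treatment in every case. Since the experimental programme begins on D4, days 1 to 3 also precede any possible difference between the arms. On the 18-day reading, 12 + 3 = 15 of the 30 days carry no between-arm effect.

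**Effect of taking a maximum.** Score at 18 days = max(worst of the 12 pre-treatment days, worst of the 18 treatment days). The first term does not depend on treatment, so it is a floor under the score.

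**At 3 months** (about 90 days) the window starts at about 90 − 30 = day 60, well after treatment ends at day 18 or 21. There is no overlap.

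**Illustration A (assumptions not in the article).** Patient mean 5 on a 0–10 scale, between-patient SD 1, independent daily SD 1.5, scores rounded and clipped to 0–10, effects in full from day 1, 100,000 simulated patients per arm. The comparator is the fall in a maximum over 18 days that does not overlap baseline.

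| Fall in pain, control vs experimental | Difference, non-overlapping maximum | Difference, last-month maximum at 18 days | Share kept |
|---|---|---|---|
| 1 vs 2 points | 1.00 | 0.15 | 0.15/1.00 = 15% |
| 0 vs 1 point | 0.97 | 0.41 | 0.41/0.97 = 42% |

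In the first row, the worst pre-treatment day exceeds the worst treatment day in 57% of control and 85% of experimental patients. A day-to-day correlation of 0.5 changes 0.15 to about 0.2. Starting the extra experimental effect on D4 lowers 0.15 to 0.12 and 0.41 to 0.32.

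**Illustration B (other assumptions, also not in the article).** Mean 5, between-patient SD 1.8, daily SD 0.5 to 2.0, a common fall of 1 point, and an extra fall of 1.5 points in the experimental arm from D4, either at once or gradually. The comparator here is the 24-hour item.

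- 24-hour item: between-arm difference 1.32 to 1.44 points.
- Last-month maximum: 0.01 to 0.35 points.
- Share kept: 1% to 26% over both visit timings, and 1% to 18% with the visit at 18 days.

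The direction is the same throughout. The size is not: it moves with the assumed effects and daily variability.

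**The case against.** The strongest reply is that the article does not commit itself to a worst-pain analysis at 18 days. The Aim section sets the pain objective at 3 months, where the window is sound. The schedule speaks of study outcomes in general and cannot mean every item at every visit, since adherence is collected at 3 months only. The repeated measures are given as examples, and EVA pain could be the 24-hour item alone. An item-by-visit table may well sit in the full protocol.

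Much of this stands. Use of the last-month item at 18 days is how the article reads, because nothing exempts it, but it is not stated item by item. The 24-hour item lies within treatment and already covers pain at that visit. The 3-month comparison is untouched. These points lower the priority, but they do not make the item suitable at 18 days if it is asked and analysed there.

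A reader might infer that the score cannot show any effect at the end of treatment. That is too strong: some of the effect was recovered in the simulations, and a worsening during treatment could still appear. A reader might also infer bias in favour of one arm, or a trial unable to detect early pain relief. Neither follows. The overlap is the same in both arms, so it shrinks a difference without favouring an arm, and the 24-hour item remains. Nor should the simulated shares be read as estimates for this trial, because none of their inputs comes from the article.

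**Conclusion.** The concern holds as a minor point about one visit of one secondary item. As the article reads, last-month worst pain at 18 days takes in about 12 pre-treatment days (9 at 3 weeks; range 7 to 13) that the baseline score already covers. As a maximum, it cannot fall below the worst of them.

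The between-arm difference at that visit is therefore attenuated, and part of any change from there to 3 months is an artefact of the recall window. The overlap in days rests only on the article's dates and the assumption that baseline is taken at the start of treatment. The amount of attenuation rests on outside assumptions: about 15% to 40% of the effect remained in one set of illustrations, and 1% to 26% in another.

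The primary outcome, the sample size, the 24-hour item and the 3-month pain comparison are not affected.

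**What to change.** State which pain item is meant in the longitudinal model. Analyse last-month worst pain at baseline and 3 months only, and let the 24-hour item carry pain at 18 days. This takes one sentence in the analysis text and works even if the data are already collected. The cost is that worst pain has two time points instead of three.

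If the questionnaire can still be changed, the alternative is a worst-pain item whose window lies wholly within treatment at the 18-day visit (for example, the last 7 days), with the same window at baseline and 3 months. That keeps three time points, at the cost of one changed or added questionnaire line.
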